#### Treatment fidelity

All three therapists deliver both the pragmatic rehabilitation and the supportive listening treatments. We chose this approach rather than having different therapists delivering the different therapies in order to reduce the confounding of therapist effects. We have a good track record in trials of CFS/ME [17] and other similar conditions [39] of achieving fidelity when the same therapist delivers more than one treatment, and we recognise the importance of maintaining treatment fidelity in this trial. With patients' permission, all nurse therapist visits and telephone calls are audio-taped, using digital recorders. We have developed a schedule for treatment fidelity ratings and have recruited three independent raters who are rating a random sample (5%) of the therapy tapes. The tapes are selected so that: (1) approximately equal numbers come from each therapist, (2) approximately equal numbers of PR and SL are represented and (3) all treatment sessions are represented, but are otherwise selected at random. Tapes are rated blind to treatment classification. Each tape is classified as one or other treatment, and receives an overall quality of therapy rating. Additionally, more detailed ratings of therapeutic alliance, generic therapy quality and treatment-specific therapy quality are produced, which will be used in subsidiary analyses.

#### Treatment adherence

Experience from the Liverpool study suggests that patients who accepted the rationale for treatment were willing to adhere to it. In the Liverpool study, treatment was completed by 127/148 patients; i.e. a drop-out rate of only 14%. On the other hand, in a trial of cognitive behaviour therapy versus counselling for fatigue in primary care [22], 44/193 (35%) eligible patients failed to complete treatment, suggesting that the likely degree of adherence in primary care may be lower than that seen in hospital care.

#### Anticipated loss to follow up

In the Liverpool study, 148 patients were randomised to treatments; each was scheduled to receive four assessments by postal questionnaire (baseline, 3 months, 6 months, one year), making a total of 592 assessments in all. At the end of the trial, 541 of these assessments had been completed (including those completed on drop-outs), giving a loss to follow up of only 9%. Our patients will be required to complete a larger battery of assessments than those in the Liverpool study, which might reduce participation rates. On the other hand, we anticipate that the fact that interventions and assessment will take place in the patients' homes in this trial will reduce both failure to adhere to treatment and failure to complete assessments. To ensure that we have sufficient numbers to test our hypotheses, we have estimated a rate of 23% combined non-compliance and loss to follow-up (this being half-way between the 35% drop out rate reported in a previous primary care trial [22], and the 9% loss to follow up in our previous trial). To reduce loss to follow-up, we plan to ask patients to nominate a relative or friend who could be contacted to help us to trace them should they move away.

Some CFS/ME patient support groups have suggested that activity may be harmful to some CFS/ME patients [4], but no adverse outcomes have been reported from previous well-conducted treatment trials that have included adequately graded activity as a component of treatment [4]. The activity programme forming part of pragmatic rehabilitation is determined collaboratively by the patient and therapist, and always starts at a level less taxing than the patient can currently manage. Similarly, the rate at which activity is increased and the type of activity undertaken are determined by the patient in collaboration with the therapist. If there are any adverse reactions, these will be notified to the independent committees overseeing the trial (the Data Monitoring and Ethics and Trial Steering Committees) and to MREC, in accordance with agreed procedures.

### Recruitment of patients

After obtaining formal approval from the relevant Primary Care Trusts, information about the trial is sent to GP practices in the North West of England. GPs are asked to identify patients whom they think may be suitable for the trial from their patient lists and from new consultations, and then to assess each patient in accordance with a protocol/checklist provided in their information pack. The checklist is based on the Oxford criteria [1] and includes a list of advised exclusionary tests. If, in the GP's opinion, the patient fulfils the trial criteria, and the patient agrees, a referral is sent to the FINE Trial office. A copy of the Patient Information Sheet and consent form is sent from the FINE Trial office to the patient, and followed up one week later by a telephone call from one of the research team (research assistant or trial manager) during which the patient can ask questions and decide whether he or she wishes to be assessed. At the baseline assessment, which takes place in the patient's home, the trial is explained again, the importance of maintaining researcher blindness is emphasised to the patient, and written informed consent is obtained. The baseline assessment is then carried out. (See Figure 1).

### The baseline assessment

The baseline assessment serves two purposes – firstly to ensure that patients recruited to the trial meet study criteria, and secondly to obtain baseline measures on all our outcomes. The schedule for the baseline assessment and subsequent assessments is shown in Table 1. If there is any doubt as to whether the patient fulfils criteria for entry to the study, the research assistant consults with medically qualified members of the team and/or the referring GP, and if necessary the patient can be referred back to the GP for further information or tests. Once we are satisfied that the patient fulfils study criteria, the trial manager notifies the randomisation service.

### Randomisation

Randomisation of individual patients as they are recruited to the trial is carried out by an independent randomisation unit based at Christie Hospital in Manchester, in consultation with the trial statistician, and in accordance with a randomisation protocol. The procedure uses randomised permuted blocks (with randomly-varying block sizes of 9, 12, 15 or 18), after stratification based on whether the patient is ambulatory or not (not ambulatory being defined as using a mobility aid on most days), and on whether the patient fulfils London ME criteria or not. There are therefore four strata in total. Where applicable, patients are assigned to therapists in a simple random fashion according to the therapists' availability. The trial manager is informed of randomisation, and group membership is conveyed to the designated nurse-therapist, if appropriate. The GP is informed of randomization and sent a copy of the patient consent form.

### Outcome measures

Patients are assessed at entry to the trial (week 0), within one week of the end of treatment (20 weeks), and then one year after finishing treatment (70 weeks). Assessments are carried out by trained researchers who are blind to the arm to which the patient has been randomised. Assessment at week 70 is required because short-term assessments of outcome in a chronic health condition such as CFS/ME can be misleading. Additionally, psychological treatments such as CBT become more effective over time [13] and we wish to be able to determine whether that is the case for our interventions. The primary outcome point is 70 weeks.

#### Primary outcome measures

The primary outcome measures are patient-rated to avoid observer bias. These are (1) score on the physical functioning scale of the SF-36 [35], (2) cost-effectiveness using the Euroqol [40] and (3) the score on the 11-item Fatigue Scale [36]. An improvement of 50% or more on the SF-36 physical functioning scale, or a score of 75% or more on that scale, will be considered a clinically significant improvement.

#### Secondary outcome measures

Secondary outcome measures are (1) time to take 20 steps, (or number of steps taken, if this is not achieved) and maximum heart rate reached on a step-test [41]; (ii) scores on the anxiety and depression scales of the HADS [42] to provide measures of depression and anxiety; (iii) scores a brief four-item sleep scale [43].

### Qualitative study

Four phases of qualitative interviews are being carried out with sub-samples of patients and GPs. These will explore GP and patient attitudes to CFS/ME, its current management, and the trial interventions. In addition, we will determine the mechanisms of action of the interventions and identify barriers to their implementation. The composition of the samples will mirror that of the quantitative study, with representatives of all three treatment groups, study participators and study refusers, while the exact size of the sub-samples will be determined during the course of analysis using the constant comparative technique [48]. The first patient sub-sample will include patients who have consented to take part in the study. We will use maximum variance sampling to generate a range of respondents in terms of age, gender, sociodemographics and ethnicity, and the sample will include patients entering each of the three treatment groups. If possible, we will also interview patients who have refused to take part in the study, but consented to be interviewed. We anticipate that approximately 40 interviews will be required. These first phase qualitative interviews, carried out after the first quantitative assessment but before treatment commences, will explore patient views on illness causation, beliefs about CFS/ME, expectations of intervention and previous experience of treatment and doctor-patient relationships, and will provide a comparison for data obtained from the post-trial qualitative interviews. A second set of interviews will be carried out towards the end of the trial, with a different subset of patients, in order to investigate the processes related to successful engagement in and response to treatment. Sub-samples of patients from the three intervention groups with good and poor outcomes on final assessment will be selected (approximately 20 of each) and will be interviewed about their experiences of the intervention, the value they place on treatment, their relationship with the therapist, and whether their views on the causation of CFS/ME changed during the course of treatment. Patients' views on the effectiveness of the treatment and their plans for management of future health problems will be sought. Particular attention will be paid to equality issues in terms of access to and experience of treatment. Thirdly, qualitative interviews with a representative sample of GPs who have referred or not referred patients to the study (approximately 10 of each) will be performed to explore barriers and drivers towards referral. Finally, the three nurse therapists were interviewed at the end of training and prior to starting treatment, and will be interviewed again at the end of the trial to ascertain their experience of being trained to deliver these treatments, and of the treatment process itself.

### The economic evaluation

A full economic evaluation is being undertaken alongside the clinical trial. The economic evaluation takes a societal viewpoint, but will also disaggregate data to enable us to examine implications for specific sectors such as primary and secondary care within the NHS as well other government agencies (for example Social Services). Resource-use data detailing the use of primary and secondary care services, social and community services, private and voluntary services are collected at each assessment point. Unit cost estimates will then be applied to each resource, using figures from local providers supplemented by national data where appropriate. For each patient in the trial, a total cost will be estimated by calculating the product of resource use and the relevant unit cost. In addition, cost to patients (e.g. travel costs) will be estimated at 70 weeks. Cost data will be analysed using appropriate statistical techniques, such as bootstrapping, and will also be subjected to extensive sensitivity analysis. A cost-utility analysis will be performed using the EQ5D [40] as a measure of health related quality of life.

The power analysis for this trial has been based on the effects expected in the clinical measures. To address the issue of the adequacy of the sample size to perform the economic evaluation, methods of presenting data that allow for the uncertainty created by potentially under-powered economic evaluations, such as cost-effectiveness acceptability curves, will be employed. These techniques allow for the cost of the uncertainty to be estimated and therefore the value of future data collection can be assessed.

### Power analysis

We plan to recruit 120 patients for each treatment arm. Our power calculation was based on a comparison between pragmatic rehabilitation and treatment as usual. In the Liverpool hospital-based study [26], at 12 months after the start of treatment, on an intention to treat basis with previous scores assigned for dropouts, 57% of intervention group patients and 6% of control group patients were classified as "no longer cases" (i.e. scored 4 or less on the Fatigue Scale and 75% or more on the SF36 physical functioning scale). On the basis of previous studies, we would expect to see a bigger improvement in patients receiving treatment as usual in primary care [7,9]. We have also taken a more conservative estimate of the proportion of patients likely to improve in the pragmatic rehabilitation condition; we believe that a 20% difference in improvement rates between intervention and control patients would be of interest to the NHS. A two-group χ^2 ^test with a 0.05 two-sided significance level will have 80% power to detect the difference between an intervention group proportion of 50% improved and a treatment as usual group proportion of 30% improved, when the final sample size is 93 per group. Allowing for a rate of loss to follow-up of 23% in the treatment as usual group, the sample size required is 120 per group.

### Analysis plan

Analysis of both the quantitative and qualitative data collected during the course of the trial will take place in accordance with pre-determined analysis plans, which have been lodged with the Data Monitoring and Ethics and Trial Steering Committees.

#### Analysis of quantitative data

Baseline comparability of the three treatment groups will be described, but no significance testing will be conducted. Acceptance of and adherence to treatment will be described. Patients in the pragmatic rehabilitation and supportive listening arms will be deemed to have accepted treatment allocation if, after randomization, they embark on treatment, that is they make themselves available for the first treatment session. Patients in the treatment as usual arm will be deemed to have accepted treatment if, after randomization, they agree to return to their GP's care. To measure adherence to treatment, in the pragmatic rehabilitation and supportive listening arms, the number of home visit sessions and number of telephone calls that in the opinion of the therapist constituted an intervention session will be counted. No attempt will be made to assess adherence further than this. In the absence of any protocol violation (e.g. receiving a systematic psychological therapy for CFS/ME), patients in the treatment as usual arm will be deemed to have adhered to treatment. Missing outcome data will be described in relation to patient baseline characteristics and adherence to treatment.

Descriptive statistics for outcome measures will be presented. The main analyses will be carried out using all patients randomized using the principle of Intention-To-Treat (ITT). With three groups (Pragmatic Rehabilitation – PR, Supportive Listening – SL and Treatment as Usual – TAU) we will have two degrees of freedom to test for group differences. Following a global test to determine whether the three groups are different, pragmatic rehabilitation will be contrasted with supportive listening. If there is no evidence of any difference in outcome between pragmatic rehabilitation and supportive listening, they will be jointly contrasted with treatment as usual. If pragmatic rehabilitation and supportive listening differ in their outcomes, then they will be separately compared with treatment as usual. Effect sizes and confidence intervals will be reported for each group

Sensitivity of the treatment effect estimates to potential biases arising from missing outcome data will be evaluated by the use of inverse probability weighting [49,50]. This assumes that the missing data mechanism is ignorable – i.e. Missing at Random (MAR). We will also carry out a likelihood-based analysis of all available data using *Mplus *[51] again assuming that the missing data mechanism is ignorable.

A supplementary set of analyses will be undertaken to assess the effect of non-adherence to allocated treatment (again taking account of sensitivity to assumed missing data mechanisms) in order to estimate treatment effects in those patients who have complied with randomization (the estimation of the Complier Average Causal Effect – CACE – as opposed to the Average Causal Effect – ACE – as estimated using ITT methods). We have provided detailed examples of this approach elsewhere [52,53].

All analyses to estimate treatment effects will be variations on an analysis of covariance with the exact form depending on whether outcome is binary or quantitative. Covariates will include whether the patient is ambulatory or not, and whether the patient fulfils London ME criteria or not.

Supplementary, exploratory analyses will be carried out to determine predictors of response to treatment. These will include, but may not be restricted to, (1) dichotomous variables such as membership of self-help group, whether ambulatory or not, whether the patient fulfilled London ME criteria, presence or absence of psychiatric diagnosis (e.g. depression); and (2) continuous variables such as illness duration, score on HAD depression scale, score on social support scale, and baseline illness beliefs scores. Analysis will take place once, after data collection is complete. There are no proposed interim analyses.

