## Discussion

Our trial will be the first randomised controlled trial of treatments for CFS/ME in primary care, and will add to the knowledge base in a number of ways. We have both a comparison treatment that controls for supportive therapist contact time and a treatment as usual control arm, which will help us to assess the efficacy of pragmatic rehabilitation. Our trial is conservatively powered, so we can be confident of detecting clinically significant effects. This is a pragmatic trial with relatively inclusive entry criteria, and we anticipate recruiting patients from across the spectrum of illness severity. Because we are treating patients in their homes, we are able to assess and treat patients who are unable to access secondary care services. These features will improve the generalisability of our findings.

We have taken a number of steps to protect our trial against sources of bias. While therapist effects are not a primary outcome measure in this trial, we have chosen to use three nurses in order to minimise, or at least observe, possible therapist effects. To counteract possible biases introduced by the place of recruitment, all three nurses treat patients recruited from across the recruitment area. Differential willingness of patients to be randomised to treatment as usual is minimised by constraining only systematic psychological therapies for CFS/ME in the treatment as usual arm of the trial. To reduce observer bias in assessment, all assessment data are collected by research assistants not involved in, and blind to, treatment; in addition, the research assistants are accommodated in different locations from the therapists. All unblindings are recorded systematically. All outcome measures except the step-test are patient-rated. Bias and random error in handling data will be minimised by validation checks by the trial manager on data entry by the research assistants.

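### The stated 80% power belongs to a direct two-group test of pragmatic rehabilitation versus treatment as usual, a test that the written analysis sequence does not make directly

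*Protocol article*

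**What the plan says.** Under Power analysis the protocol article states: "Our power calculation was based on a comparison between pragmatic rehabilitation and treatment as usual". The calculation is a two-group chi-square test at the two-sided 5% level with 80% power. The rates it assumes are "an intervention group proportion of 50% improved and a treatment as usual group proportion of 30% improved", and the number needed is given as 93 evaluable in each arm. Allowing for 23% loss, this becomes 120 per arm. No improvement rate for SL appears.

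Under Analysis of quantitative data, with three arms, "we will have two degrees of freedom to test for group differences". The order of testing is then given: "Following a global test to determine whether the three groups are different, pragmatic rehabilitation will be contrasted with supportive listening". What follows depends on that contrast. If PR and SL show no difference, they are combined and set against TAU. If they differ, each is compared with TAU on its own. The section gives no level for the global test and does not say that testing stops if it is not significant.

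Under Aims of the study, the first two principal questions are PR versus TAU and SL versus TAU. PR versus SL is listed among further issues. The Discussion says: "Our trial is conservatively powered, so we can be confident of detecting clinically significant effects".

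**The concern.** The sample size section and the analysis section describe different tests. The sizing test has one degree of freedom and compares PR with TAU directly. In the written sequence that comparison sits behind a three-group test with two degrees of freedom and then behind a PR versus SL contrast. Each step can prevent a separate PR versus TAU result that would have been significant on the test used for sizing.

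Two things are at stake. First, the 80% may not describe the chance of success under the procedure to be followed. Second, when PR and SL are not distinguished, the plan answers a different question from principal question 1: the combined effect of PR and SL instead of the effect of PR. For example, with PR at 50% and SL at 30%, the pooled rate is (50 + 30)/2 = 40%, so the contrast with TAU at 30% is half the effect the trial was sized for.

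**Working it through.** **Inputs from the Power analysis section:** PR 50%, TAU 30%, two-sided 5%, 80% power, 93 evaluable per group, 23% loss, 120 recruited per arm. **Assumed:** an SL rate of 30-50% (between the two stated rates), since none is given; unadjusted binary outcome; every test at two-sided 5%.

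**1. Reproduce the stated figure.** Pooled-variance formula without continuity correction:

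n = [1.96 × √(2 × 0.4 × 0.6) + 0.8416 × √(0.5 × 0.5 + 0.3 × 0.7)]² / 0.20² = (1.358 + 0.571)² / 0.04 ≈ 93.

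Power at 93 per group is 80.0%. For loss, 93/0.77 = 120.8 and 120 × 0.77 = 92.4, so 120 agrees within rounding. The stated figures are correct for the test named.

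**2. Compare that test with the global test.** Noncentrality of the two-group test: 93 × 0.20² / (2 × 0.4 × 0.6) = 7.75, referred to 3.84 (1 df). For the global test it is n × Σ(pᵢ − p̄)² / [p̄(1 − p̄)]. With SL at 40% this is 93 × (0.1² + 0 + 0.1²) / (0.4 × 0.6) = 7.75, referred to 5.99 (2 df). With the same noncentrality and a higher threshold, power is 70.3%.

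**3. Follow the written sequence.** Global power is from the non-central chi-square. The other columns come from 400,000 simulated trials per SL rate, 93 per arm, Pearson tests without correction. A direct PR versus TAU test has 80% power in every row.

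| SL rate (assumed) | Global noncentrality | Global test significant | PR v SL significant | Global and PR v TAU both significant | Written path, gated: separate PR v TAU significant | Written path, gated: benefit by either branch | Same, no gate |
|---|---|---|---|---|---|---|---|
| 30% | 10.68 | 84% | 80% | 75.9% | 68% | 75% | 76% |
| 35% | 8.52 | 75% | 54% | 71.6% | 48% | 70% | 73% |
| 40% | 7.75 | 70% | 27% | 69.5% | 25% | 68% | 76% |
| 45% | 8.29 | 73% | 10% | 71.6% | 9% | 73% | 83% |
| 50% | 10.10 | 82% | 5% | 75.6% | 3% | 81% | 89% |

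Either branch means PR alone v TAU when PR and SL differ, and PR and SL pooled v TAU when they do not.

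**4. Read the table.** The gate by itself costs the PR versus TAU test about 4 to 10 points (80 − 75.9 = 4.1; 80 − 69.5 = 10.5). The PR versus SL step costs a separate PR versus TAU result far more as SL approaches PR. Without the gate, a separate comparison is still made only as often as PR v SL is significant, 80% down to 5%.

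**5. Sensitivity.** With SL at 25% or 55%, the global-and-PR-v-TAU figure is about 79%. If all 120 per arm were evaluable, it would be about 81-87% for SL 30-50%.

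**The case against.** **The gate is inferred.** The step from the global test to PR versus SL carries no condition, while the two later steps do, and no level or stopping rule is given. The article says that analysis plans were lodged with the oversight committees, and these may settle the matter. This stands: without a gate, the loss from the global step does not arise. It does not remove the point, because the article itself makes the PR versus SL result decide whether PR is compared separately with TAU.

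**A reader might infer that the plan simply has 70-76% power for PR versus TAU, whatever rule governs PR versus SL.** The documents do not support that. The range needs a strict 5% gate and an SL rate the article does not give, and it describes a route, global test and then PR versus TAU, that the plan does not contain. On the written path the result depends heavily on the PR versus SL rule. With SL at 50%, benefit by either branch reaches 81%, so nothing is lost on that measure.

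**A global test before pairwise tests is a recognised way to control error with three groups.** This stands. The sequence is not illegitimate in itself, but the stated power should then belong to it.

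**The sizing has reserves.** The section on anticipated loss to follow-up describes the 23% as non-compliance and loss combined, and under intention to treat non-compliers with outcome data stay in. The assumed effect is also far smaller than the 57% v 6% of the earlier hospital trial. Both are fair, and they support caution about the assumed effect and loss. Neither makes the 80% at 93 per group the power of the written sequence.

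**Conclusion.** The mismatch holds. The 80% is correctly calculated for a direct two-group test of PR versus TAU, but it is not the power of the procedure in the analysis section. With 93 evaluable per arm, the unadjusted binary outcome, SL between 30% and 50%, and the global test read as a strict 5% gate:

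- global test and PR versus TAU both significant: about 70-76%;
- benefit over TAU by either branch of the written path: about 68-81%;
- significant separate PR versus TAU result on the written path: about 3-68%.

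These figures illustrate the size of the mismatch; they do not predict the power of the final analyses. The clinical primary outcomes are scale scores and the models are covariate-adjusted, so actual power may differ. It would be too strong to call the trial underpowered outright: the shortfall depends on the gate, the SL rate and the number evaluable.

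**What to change.** **Preferred.** In Analysis of quantitative data, make PR versus TAU a direct test at two-sided 5% for each primary outcome, as sized, followed by SL versus TAU at 5% if the first is significant. Report the global test, the PR versus SL contrast and any pooled contrast as supporting analyses. This replaces the conditional pooling rule. It controls error over the two comparisons within each outcome only, not across the several primary outcomes.

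**Alternative.** Keep the sequence, state whether the global test is a gate and at what level, and restate the power for the procedure actually used, with the assumed SL rate. The Discussion's claim of conservative power should then be limited to the assumed effect size.

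**Cost.** Wording only; no extra patients or data. Under the preferred option, SL versus TAU is confirmatory only after PR versus TAU has succeeded. Under the alternative, the stated power may be less favourable. The article plans one analysis after data collection and no interim analyses, so either change can be made before results are seen.

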### Aims of the study

This study was designed to address four principal research questions:

(1) Is pragmatic rehabilitation, delivered at home by nurses to CFS/ME patients recruited from primary care, a clinically effective intervention in terms of reduced disability and fatigue when compared with treatment as usual delivered through the primary care team?

(2) Is supportive listening, delivered at home by nurses to CFS/ME patients recruited from primary care, a clinically effective intervention in terms of reduced disability and fatigue when compared with treatment as usual delivered through the primary care team?

(3) Which of the three treatments, pragmatic rehabilitation, supportive listening and treatment as usual, is the most cost-effective?

The study will also address three further issues: the relative efficacy and cost-effectiveness of pragmatic rehabilitation and supportive listening; the mechanism of action of these treatments; and barriers to the implementation of these treatments in UK primary care settings.

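### Whether each therapy is compared with treatment as usual on its own depends on an unpowered test of the two therapies against each other; a non-significant result leads to pooling

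*Protocol article*

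**What the plan says.** All references are to the protocol article.

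- **Aims of the study.** Two separate principal questions are put, each against treatment as usual (TAU). One is for pragmatic rehabilitation (PR): "Is pragmatic rehabilitation, delivered at home by nurses to CFS/ME patients recruited from primary care, a clinically effective intervention". One is for supportive listening (SL): "Is supportive listening, delivered at home by nurses to CFS/ME patients recruited from primary care, a clinically effective intervention". The comparison of the two therapies with each other is only among the further issues: "the relative efficacy and cost-effectiveness of pragmatic rehabilitation and supportive listening".
- **Power analysis.** "Our power calculation was based on a comparison between pragmatic rehabilitation and treatment as usual". The inputs are 50% against 30% improved, two-sided 5%, 80% power and 93 evaluable patients per group.
- **Analysis of quantitative data.** The order of testing is: "Following a global test to determine whether the three groups are different, pragmatic rehabilitation will be contrasted with supportive listening". Then: "If there is no evidence of any difference in outcome between pragmatic rehabilitation and supportive listening, they will be jointly contrasted with treatment as usual". The alternative branch is: "If pragmatic rehabilitation and supportive listening differ in their outcomes, then they will be separately compared with treatment as usual". The paragraph ends: "Effect sizes and confidence intervals will be reported for each group".

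No significance threshold, equivalence margin or power is stated for PR against SL. The article also does not say whether the global test must be significant before the next step is taken.

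**The concern.** The order of the analysis reverses the order of the aims. A comparison that the aims treat as a further issue, and that the sample size was not built for, decides whether the two principal questions are tested separately or merged into one.

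The natural reading of the rule is that a non-significant PR-SL test leads to pooling. Such a result is what one expects when the therapies are equal, but also when they differ by an amount the trial is too small to detect. In the second case the joint contrast estimates an average of two different effects. It answers neither principal question, and the contrast for which the trial was powered is not made on its own. The Discussion expects a successful result to shape training and services in primary care, and a single averaged effect cannot show which therapy earned it.

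**Working it through.** **1. Reproduce the plan's figure.** Two-proportion chi-square without continuity correction, 50% against 30%:

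n = [1.96·√(2·0.40·0.60) + 0.8416·√(0.50·0.50 + 0.30·0.70)]² / 0.20² = (1.358 + 0.571)² / 0.04 = 93 per group.

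This agrees with the article. Allowing for 23% loss, 93/0.77 = 120.8, against 120 stated; the difference is immaterial here.

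**2. Power of the deciding test, PR against SL, at 93 per arm.**

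Power = Φ{[√93·(p₁ − p₂) − 1.96·√(2p̄(1 − p̄))] / √(p₁(1 − p₁) + p₂(1 − p₂))}, with p̄ the mean of p₁ and p₂.

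PR is held at the article's 50%. The article gives no SL rate, so a range is assumed. For SL at 40%: (0.964 − 1.379)/0.700 = −0.592, so power is 28%.

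| SL rate (assumed) | PR-SL power | Trials that pool (1 − power) | Evaluable n per arm for 80% power |
|---|---|---|---|
| 45% | 10% | 90% | 1565 |
| 40% | 28% | 73%* | 388 |
| 35% | 54% | 46% | 170 |
| 30% (same as TAU) | 80% | 20% | 93 |

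*72% by the formula, 73% in simulation. The pooling column does not require the global test to be significant.

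The Background says patients can be expected to benefit from SL. The plan itself therefore points to a PR-SL gap smaller than the PR-TAU gap, which is where the test is weak.

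**3. Follow the whole sequence.** 400,000 simulated trials per scenario, 93 per arm, binary outcome, every test at two-sided 5%. Where a range is given, it covers requiring and not requiring a significant global test.

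- *PR/SL/TAU = 50/40/30% (SL assumed).* Pooling occurs in 73% of all trials, and in 63% of those with a significant global test. The pooled estimate averages (50 + 40)/2 − 30 = 15 points, or about 19 if the global test must be significant. The true effects are 20 and 10. A separate, significant PR-TAU result is reached in about 26% of trials, against 80% if that contrast is always tested.
- *50/30/30% (SL inert, assumed).* About 20% of trials pool, or about 10% of those passing the global test. If a significant joint result is read as applying to each therapy, SL is credited with benefit in 7.6–8.3% of trials, against a one-sided nominal 2.5%. On the same reading PR is credited in 75–76%, against 80% by direct test.
- *50/50/30% (therapies equal, assumed).* About 95% pool, so the separate questions are almost never tested. Here pooling is harmless to the estimate, and the joint contrast is significant in the right direction, or the separate one is, in 81–89% of trials.

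**4. Dependence on scale.** The primary clinical outcomes are scale scores, and the article gives no standard deviations. If 50% against 40% is translated to a standardised difference of 0.25 on a probit scale (an assumption, without baseline adjustment), PR-SL power at 93 per arm is about 41%, and pooling occurs in about 59% of trials. About 245 per arm would be needed for 80% power.

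**The case against.** The strongest defence is that the rule is prespecified and has a logic: it splits the two degrees of freedom into PR against SL and active therapy against TAU. If the therapies are equal, pooling gains power. If all three arms are equal and the global test must be significant, SL is falsely credited in only about 1.5% of trials (one-sided). Per-group effect sizes and confidence intervals are promised, and fuller analysis plans were lodged with the oversight committees and may say more. All of this is fair. But the per-group sentence names no contrast with TAU and does not restore the comparisons that the rule withholds, and the printed rule is explicit.

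Four stronger readings are tempting and are not supported:

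- *That the plan will declare an inert therapy effective.* The article does not say that a significant joint contrast will be read as proof for each therapy. The 8% figure, and any claim of bias for each therapy, holds only under that reading.
- *That the PR-SL test is weak in all cases.* Its power is 80% if SL is no better than TAU. The weakness concerns smaller gaps.
- *That the figures come wholly from the plan.* The 93 per arm, 50% and 30% do. Every SL rate is assumed, and the outcome simulated is unadjusted and binary. Adjusted analysis of the scale scores may have more power.
- *That sharing nurses between the therapies blurs them and so favours pooling.* The article reports no contamination. It describes recorded sessions, independent raters blind to treatment classification, and separate supervision for each therapy.

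**Conclusion.** The point holds. The analysis rule conflicts with the aims and with the power analysis: a non-significant result on a further issue can replace two principal questions by one averaged contrast. Over assumed SL rates from 45% down to 30%, this happens in about 90% to 20% of trials before any requirement on the global test. Requiring a significant global test lowers the frequency but does not remove the fault: at 50/40/30%, 63% of the trials that pass it still pool, and the pooled estimate then lies further above SL's true effect.

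The sizes rest on the article's binary power inputs, on assumed SL rates, and on reading an absence of evidence as non-significance at two-sided 5%. On the continuous scores pooling may be less frequent. The logical fault, treating failure to find a difference as equality, is the same on either scale.

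**What to change.** Delete the conditional pooling. From one three-arm model, always estimate and test PR against TAU and SL against TAU separately, with 95% confidence intervals, whatever PR against SL shows. Report PR against SL as secondary, with its interval and no equivalence reading of a non-significant result. Any pooled contrast is supplementary only.

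Prespecify a multiplicity approach that does not make the SL question depend on the PR result. Holm's procedure would do. So would testing the two contrasts only after a significant global test, which is sufficient with three arms. A fixed sequence with PR first is not suitable, because SL against TAU is a principal question in its own right. If only SL worked (50% against 30%), that sequence would detect it in about 3% of trials, against about 75% under the present rule. If both worked, it would detect SL in 69%, against 81–89%.

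**Cost.** The change is to wording and needs no extra patients if the following is accepted. Without adjustment, PR-TAU power stays at 80% with 93 per arm, whatever SL does. What is lost is the gain from pooling when the therapies are truly equal (81–89% against 80%). Multiplicity adjustment takes somewhat more. Under Holm the least favourable case is a test at 2.5%: (1.929 − 2.241·0.693)/0.678 = 0.554, so power is about 71%. If the global test must be significant, power cannot exceed that of the global test itself, which is about 71% at 50/40/30% and 84% at 50/30/30%.
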